Patient follow ups: Effectiveness of SBIR intervention	Patients’ behavior change status for both control and intervention patient groups	Intention to change behavior, awareness about the problem, commitment to action, uptake to referral programs, active modification of behavior (such as quit attempt, reduce/quit tobacco use, reduce/stop alcohol intake, and initiate/increase physical activity). Covariates for effectiveness outcomes: Sociodemographic/socioeconomic (such as age, sex, marital status, ethnicity, education, employment, income, rurality, immigration-related factors) and overall physical and mental health status.	Primary data collection from patients.	Follow-up telephone interview at six months of index hospitalization discharge/visit. Data collection tool will include the questionnaires guided by the Prochaska model of change process and the risk factor screening questions included in the Connect Care

Healthcare resource use	Hospital readmissions and emergency visits for both control and intervention patient groups	Hospital readmissions and emergency visits during the year after index hospitalization discharge /visit. Reasons/diagnosis for readmissions and emergency visits, and family physician/primary care visits within 1-year of discharge/visit and diagnoses/comorbidities at the time of recruitment to 1-year of index hospitalization discharge/visit.	Administrative health databases: Discharge Abstract Database, National Ambulatory Care Reporting System, and physician claim databases	Data from multiple databases will be accessed through Data and Analytics. and will be linked with the follow-up interviews using the personal health numbers.

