Health care utilization measures include hospital readmissions and emergency visits within one year of the index discharge/visits. These outcomes are of particular importance to facilitate outcome comparisons with other studies as well as because they are important to provide cost-effectiveness assessments to support intervention spread/scale decisions by health system administrators. The health care utilization data will be obtained from linked administrative health databases accessed through the Department of Data and Analytics, the custodian of these routinely collected healthcare data (Table 1).

Data on potential confounding variables including sociodemographic and socioeconomic status for both groups are collected during the 6 months patient follow-up interviews. Diagnosis and comorbidity related variables will be obtained from the administrative health databases. A detailed data collection plan is shown in data collection matrix (Table 1).

*Sample size:* SBIR intervention can increase smoking quit rate at 6-months by 11% [40], reduce alcohol misuse rate at 5-months by 19% [41], and increase patients’ average daily physical activity level by 22% [42]. Based on sample size estimation in relation to tobacco use (with effect size of 11%), we will need a maximum of 1,000 patients in each group (a total sample of 2,000 for controlled and intervention groups) to detect the smallest difference, among all outcomes, between the groups (with a study power of 80% and alpha of 0.05). This is the maximum number needed since tobacco is the least prevalent condition and it will also have the smallest proportion of change in behaviour after intervention, among the three risk factors. We will recruit a total sample of 4,000 (2,000 sample for controlled group and 2,000 for intervention group) to account for the anticipated 50% loss to follow up or nonresponse rate. The expected dropout rate is determined based on our previous paper-based SBIR pilot study [22].

*Analysis:* We will use log-binomial regression models to estimate risk difference and relative risk (for health behaviour change outcomes), and Cox proportional competing risk regression models to estimate hazard rate difference and hazard ratio (for health care use outcomes), to compare outcomes between the two groups adjusting for confounders, such as reasons or diagnosis for visits/admissions, comorbidity, and socioeconomic status.

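### Socioeconomic and self-rated health covariates come only from the 6-month call that about half the patients miss, and comorbidity is extracted to one year after index, so the adjusted utilization model risks avoidable patient loss and post-index adjustment

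*Protocol article*

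**What the plan says.** In the protocol article, under the effectiveness research plans, the timing of the confounders is explicit: "Data on potential confounding variables including sociodemographic and socioeconomic status for both groups are collected during the 6 months patient follow-up interviews". Table 1 agrees. The behaviour-change row lists "Covariates for effectiveness outcomes: Sociodemographic/socioeconomic (such as age, sex, marital status, ethnicity, education, employment, income, rurality, immigration-related factors", together with "overall physical and mental health status", and its collection method is "Follow-up telephone interview at six months of index hospitalization discharge/visit". The article describes no collection of this block at enrolment.

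Clinical covariates have another source: "Diagnosis and comorbidity related variables will be obtained from the administrative health databases". The Healthcare resource use row of Table 1 gives their window as "diagnoses/comorbidities at the time of recruitment to 1-year of index hospitalization discharge/visit". The same row says that the administrative data "will be linked with the follow-up interviews using the personal health numbers".

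The Analysis paragraph plans a Cox competing-risk model for health care use, adjusted for confounders such as diagnosis or reason for visit, comorbidity and socioeconomic status. Readmissions and emergency visits are counted over one year from the index discharge or visit.

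The Sample size paragraph doubles recruitment "to account for the anticipated 50% loss to follow up or nonresponse rate". The Expected Results section reports that response is running at about 50%.

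**The concern.** The utilization outcome is known from administrative data whether or not a patient answers the telephone. Part of the adjustment set for that outcome is known only for those who do. Three problems follow if the text is applied as it stands.

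- **Avoidable loss.** Patients with a known outcome but no interview lack the socioeconomic covariates that the model needs.
- **Selection after time zero.** The outcome clock starts at index, but a full covariate record requires being alive, reachable and willing six months later. A patient who dies earlier, which is a natural competing event in the planned model, has no interview data.
- **Adjustment for later events.** Employment, income and self-rated health at six months are measured after the intervention and halfway through the outcome year. An early readmission could change any of them. A comorbidity window that runs through the outcome year can pick up diagnoses made at the very readmissions being modelled.

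The comparison is non-randomised and separated in time, so covariate adjustment is its main protection against confounding. The utilization estimates also feed the cost analysis intended for decisions on spread and scale.

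**Working it through.** **Inputs from the protocol article.** 1,000 needed per group; 50% anticipated loss; target 2,000 per group and 4,000 in total; power 80%, alpha 0.05 (taken here as two-sided, since the article does not say). To date: 2,015 controls, of whom 1,000 have completed the 6-month call; 175 intervention participants, of whom 75 have completed it.

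**Assumed, because the article gives no figure.** One-year event proportion 15%, 30% or 50%; hazard ratio 0.85.

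**1. The plan's own figure.** 1,000 / (1 − 0.50) = 2,000 per group, which matches the target. The inflation protects the tobacco outcome. It does not address the utilization model.

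**2. Follow-up to date.** Controls 1,000/2,015 = 49.6%; intervention 75/175 = 42.9%; together 1,075/2,190 = 49.1%. These are lower bounds. The 1,015 controls without a completed call (2,015 − 1,000) may include patients not yet due, since three of the eight sites are still in their control period.

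**3. Patients left under complete cases.** 0.50 × 4,000 = 2,000. Standard error ratio √(4,000/2,000) = 1.41.

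**4. Power for the hazard ratio (Schoenfeld, equal groups).** Power = Φ(√D/2 × |ln HR| − 1.96), where D is the number of events and |ln 0.85| = 0.1625. At 30% events:

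- 4,000 patients: D = 1,200; √1,200/2 × 0.1625 = 2.815; Φ(0.855) = 80%.
- 2,000 patients: D = 600; √600/2 × 0.1625 = 1.990; Φ(0.030) = 51%.

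| Assumed event proportion | Power at HR 0.85, 4,000 patients | Power at HR 0.85, 2,000 patients | Detectable HR at 80% power, 4,000 | Detectable HR at 80% power, 2,000 |
|---|---|---|---|---|
| 15% | 51% | 29% | 0.80 | 0.72 |
| 30% | 80% | 51% | 0.85 | 0.80 |
| 50% | 95% | 73% | 0.88 | 0.84 |

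The detectable hazard ratio is exp(−(1.96 + 0.84) × 2/√D).

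**5. Detectable reduction in risk from 30%.** Solve d = (1.96 + 0.84) × √{[0.30 × 0.70 + (0.30 − d)(0.70 + d)]/n}. With n = 2,000 per group, d is about 4.0 points; with n = 1,000, about 5.6 points.

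**6. Can selection mislead as well as cost precision?** Suppose there is no true effect, a 30% risk in both groups and 50% response in each.

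- Response unrelated to events in controls, but 40% with an event and 54.3% without in the intervention group: observed risk there is 0.30 × 0.40 / (0.30 × 0.40 + 0.70 × 0.543) = 0.24, so RR = 0.24/0.30 = 0.80.
- The same with 45% and 52%: RR = 0.90.
- Response depends on events equally in both groups: RR = 1.0.

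Bias of this kind therefore needs differential dependence. The article neither shows it nor rules it out.

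**7. Comorbidity look-forward.** In a simple Cox simulation under assumed inputs, replacing a baseline comorbidity flag by one reading a year forward moved a true HR of 0.80 to about 0.81. This is the smaller part of the problem.

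**The case against.** The strongest reply is that the article nowhere states a complete-case analysis or limits the Cox model to interviewees. The confounder list is open-ended, and the handling of missing covariates may sit in an analysis plan that is not shown. That stands: the loss of half the patients is conditional. But imputation would have to fill the whole interview block for about half the cohort, and no method creates baseline values that were never taken.

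A reader might infer that attrition in the behaviour outcomes cannot be modelled at all. The article does not support this. Risk screening at recruitment, unit, recruitment period and administrative diagnoses exist for every enrolled patient. Correction is poorer without socioeconomic data, but it is available.

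A reader might also take the 1,015 controls without a call as lost. Some may not yet be due.

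On comorbidity, Table 1 is a data-collection table. Its window includes the time of recruitment, and the same cell covers reasons for readmission, which require post-index data. It does not say that post-index diagnoses enter the model. It also sets no limit that keeps them out, so the text needs one, although the likely effect is small.

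The article makes no power claim for utilization, and 1,000 analysed per group meets its own stated need. The reduced power is therefore a lost opportunity, not a missed requirement. Several listed covariates, such as age, sex, ethnicity and education, hardly change in six months; the post-intervention concern is about employment, income and health status.

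**Conclusion.** The point holds in conditional form. The article fixes sociodemographic, socioeconomic and self-rated health covariates at a 6-month call that about half the patients miss, and gives a diagnosis window covering the whole outcome year, while the utilization model adjusts for socioeconomic status and comorbidity.

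Under complete cases, about 2,000 of 4,000 patients with known outcomes drop out of the adjusted model. At an assumed 30% event risk, the detectable reduction goes from about 4.0 to 5.6 points. The power loss at HR 0.85 ranges from 51% down to 29% (15% events) to 95% down to 73% (50% events). Patients who die or cannot be reached before six months would be excluded. The size of any resulting bias is unknown: it is nil if response depends on events alike in both groups. No figure can be put on the effect of adjusting for 6-month employment, income or health status.

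The calculation rests on complete cases, 50% response at the full target, and event proportions and a hazard ratio that are not in the article.

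**What to change.** 1. Run the utilization analysis on all enrolled patients, linking the administrative data to the enrolment list and not to the interview file. Use a primary adjustment set measured the same way in both groups at or before index: age, sex, and rurality or area-level deprivation as far as the linked data hold them, plus index diagnosis, baseline risk screening and unit.
2. Define comorbidity from a fixed look-back ending at the index date. Keep post-index diagnoses only for describing the reasons for readmissions and visits.
3. Do not adjust the utilization model for health status, employment or income taken at six months, except in a sensitivity analysis.
4. Weight the behaviour analysis for non-response, using the same baseline variables.

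The covariate block may also be collected at consent for the remaining participants, but this needs care. Controls already number 2,015 against a target of 2,000, while 175 of 2,000 intervention participants are enrolled. The change would therefore give enrolment values mainly to one group and leave 6-month values in the other. Such data should not replace the 6-month values in one arm only; they should serve non-response weighting or sensitivity analysis.

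The cost is a revised data extract and coarser, area-level socioeconomic adjustment in the primary utilization model. No additional patients are needed.

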Cost-effectiveness analysis will document the economic value of the SBIR intervention in order to communicate that value to decision-makers. Cost reduction/avoidance within one year, attributable to SBIR, will be estimated based on the reduction in 1-year readmissions and emergency visits, compared to the non-intervention comparison group. Estimates of this economic impact will be provided by applying hospitalization and emergency visit cost data, provided by Canadian Institute of Health Information (CIHI), to the utilization estimates from the above-mentioned models. Intervention implementation cost data are being collected throughout the project.

*Ethical considerations:* This study has received ethics approval from the Health Research Ethics Board of Alberta – Community Health Committee- at the University of Calgary (HREBA.CHC-22-0058).

*Involvement of people with lived experience:* IPiC-Health project has 7 patient advisors, who closely work with the research and innovation team of IPiC-Health project. The patient advisors provide insights based on lived experience to inform SBIR pathways, the research and implementation plan, development of resources, brief conversation scripts, and provide advice on acceptability and appropriateness on all aspects of the research and intervention. The Patients advisors consist of individuals connected to the Alberta Strategy for Patient Oriented Research SUPPORT Unit (AbSPORU) and Patient and Community Engagement Research (PaCER) | University of Calgary-trained patient researchers who have lived experience of care in Alberta’s patient care settings and/or with the risk factors targeted by the SBIR intervention.

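### The cost step needs numbers of readmissions and emergency visits avoided, but the Cox competing risk model it draws on, as usually read, does not determine them, and its hazard rate difference is not a model parameter

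*Protocol article*

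**What the plan says.** All of this is in the Protocol article, section Research plans for evaluation of intervention effectiveness outcomes.

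- **Outcome:** "Health care utilization measures include hospital readmissions and emergency visits within one year of the index discharge/visits". The text does not say whether the first event or every event is analysed.
- **Model for health care use:** "Cox proportional competing risk regression models to estimate hazard rate difference and hazard ratio (for health care use outcomes"), with adjustment for confounders.
- **Model for behaviour change:** "We will use log-binomial regression models to estimate risk difference and relative risk (for health behaviour change outcomes").
- **Quantity to be costed:** "Cost reduction/avoidance within one year, attributable to SBIR, will be estimated based on the reduction in 1-year readmissions and emergency visits", relative to the comparison group.
- **Route to that quantity:** "applying hospitalization and emergency visit cost data, provided by Canadian Institute of Health Information (CIHI), to the utilization estimates from the above-mentioned models".

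The Cox competing risk models are the only models named for health care use, so the last item can refer only to them. The section names no count model, recurrent-event model, additive-hazards model, baseline-hazard estimation or standardisation.

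**The concern.** A cost per hospitalization or per emergency visit becomes a saving only when multiplied by a number of events avoided. One patient can be readmitted, or return to the emergency department, several times in a year. A Cox competing risk model is ordinarily a model of time to first event. Its output is a hazard ratio and, with more work, the probability of having had at least one event. Neither says how many visits follow the first.

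The hazard rate difference raises a related problem. The model multiplies an unspecified baseline hazard by a constant, so the ratio is a parameter and the difference is not.

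The economic result is at stake. The section says the utilization outcomes matter because they feed cost-effectiveness assessments for administrators deciding on spread and scale. If first-event output is turned into a saving, repeat visits drop out, and the error can go in either direction.

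**Working it through.** The plan states no figure on this point, so there is none to reproduce. The check asks whether the named models determine the named quantities. All rates below are assumptions, because the documents give no event rates.

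**1. Hazard rate difference.** Under proportional hazards, h1(t) − h0(t) = h0(t) × (HR − 1). With HR = 0.8:

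| Baseline hazard per year | Difference per year |
|---|---|
| 0.2 | 0.2 × (−0.2) = −0.04 |
| 0.5 | 0.5 × (−0.2) = −0.10 |
| 1.0 | 1.0 × (−0.2) = −0.20 |

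One hazard ratio goes with many differences. A difference can be derived only after the baseline hazard is estimated, and it then varies with time and covariates.

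**2. Visits avoided, with the first-event effect held fixed.** Let the first event occur at constant rate r1 (0.5 per year in control, 0.4 in intervention, so HR = 0.8), and let later events occur at rate r2. Death is ignored to keep the illustration simple.

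- Probability of at least one event in a year: P = 1 − exp(−r1). Control 0.3935, intervention 0.3297. The difference is 0.0638, or about 64 patients per 1,000.
- Expected time remaining in the year after the first event: R = 1 − P/r1. Control 1 − 0.3935/0.5 = 0.2131. Intervention 1 − 0.3297/0.4 = 0.1758.
- Mean events per patient: P + r2 × R.

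| Later rate, control / intervention | Mean, control | Mean, intervention | Avoided per 1,000 |
|---|---|---|---|
| 0.5 / 0.4 | 0.500 | 0.400 | 100 |
| 1.5 / 1.5 | 0.713 | 0.593 | 120 |
| 1.5 / 0.75 | 0.713 | 0.462 | 252 |
| 0.5 / 1.2 | 0.500 | 0.541 | −41 |

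A simulation with 400,000 patients per arm gave 101, 117, 252 and −41, with a first-event difference of 63 to 65 per 1,000 throughout. A first-event analysis would look the same in all four rows, while the quantity to be costed changes in size and, in the last row, in sign.

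**3. Log-binomial model.** Take two equally common covariate strata with assumed baseline risks 0.10 and 0.30 and a relative risk of 1.5. The implied risk differences are 0.10 × 0.5 = 0.05 and 0.30 × 0.5 = 0.15, so no single risk difference is a coefficient. Their average over the strata, 0.10, is a valid standardised risk difference from the same model. A simulated fit (relative risk 1.48) returned 0.048, 0.145 and a standardised 0.097. Here the only thing missing is a statement of the extra step.

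**The case against.** Nowhere does the article say first event. It defines the outcomes as readmissions and emergency visits within a year, and Table 1 plans to collect them over the whole year from administrative databases. A recurrent-event extension of the Cox model, with an estimated mean function, could supply the counts. A time-specific hazard difference follows once the baseline hazard is estimated, and an adjusted risk difference can be standardised from a log-binomial fit. A condensed article may leave such derivations to an analysis plan that is not shown. The cost paragraph also never says that a hazard ratio will be multiplied by a cost.

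Much of this stands, and it rules out several stronger readings that a reader might infer:

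- **That the log-binomial model gives no risk difference, or that Cox can give no hazard difference at all.** Both can be derived. They are simply not parameters of the models.
- **That the cost analysis is impossible.** It is not, if all events are modelled suitably.
- **That the plan treats hazard ratios as count ratios.** The text does not say so.

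The objection does not remove the core. The article does more than leave a derivation unstated: it names a model for health care use, names the quantity to be costed, and says the second comes from the first. On the usual meaning of the named model, it does not. An analysis plan that followed the article literally would inherit the mismatch, and one that repaired it would depart from the published method.

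**Conclusion.** The point holds in limited form. The cost step relies on output from a model that, on its usual time-to-first-event reading, does not determine the number of recurring readmissions and visits avoided. In the illustration, one first-event hazard ratio of 0.8 is compatible with anything from 252 visits avoided to 41 visits added per 1,000 patients. Those numbers rest on assumed rates and show only that the quantity is not identified. They do not estimate the error in this study.

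Another figure that may tempt a reader is the share of events beyond the first. For negative-binomial counts it is (μ − P)/μ with P = 1 − (k/(k + μ))^k. With k from 0.5 to 2, that is 32–46% at an assumed mean of 0.6 per year and 49–62% at 1.2. It shows how much utilization a first-event analysis leaves out. It is not the bias in the savings, whose size and direction the documents do not allow one to state.

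The hazard rate difference is a mis-specified summary measure and should be replaced. The log-binomial risk difference is a minor matter of wording.

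**What to change.** - **Cost step:** model all readmissions and, separately, all emergency visits within one year of the index discharge or visit, using a count or recurrent-event mean model that treats death as a terminal event. Standardise over the confounders to obtain the adjusted difference in mean events per enrolled patient over one year, multiply it by the CIHI unit costs, and give bootstrap intervals. A days-at-risk offset alone is not enough, because it yields events per unit of time alive, whereas the saving is per enrolled patient and depends on survival.
- **Time to first event:** keep the Cox competing risk model, state that it concerns the first event, and report the one-year cumulative-incidence difference beside the hazard ratio in place of the hazard rate difference.
- **Behaviour outcomes:** state that the risk difference is obtained by standardisation from the log-binomial fit.

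The cost is analysis wording and one additional model per utilization outcome. The linked administrative data in Table 1 already cover the events, no further patients are needed, and the article says analysis awaits complete data, so the change can still be specified in advance.
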